### Secondary objectives

1) To determine whether the PCRM-CI model for persons with hip fracture and CI results in: i) improved mobility at 6 months post-discharge from inpatient rehabilitation; ii) greater improvement in physical functioning at the time of discharge from inpatient rehabilitation and at 6 months post-discharge; iii) a higher proportion of patients returning to their previous living situation in the community at discharge and at 6 months post-discharge.

2) To determine whether the PCMR-CI model results in similar improvements in mobility at discharge from inpatient rehabilitation and 6 months post-discharge for patients with and without CI.

3) To evaluate whether the PCMR-CI model improves HCPs’ attitudes, knowledge, satisfaction, and stress, in caring for patients with CI.

4) To examine the processes by which the PCRM-CI model is implemented by describing: i) the evidence based components of the model that facilities adopt (*i.e.*, how rehabilitation staff in the facilities decide which components they will and can replicate); ii) the context (*i.e.*, evaluation of the preparedness of the context to embrace and sustain implementation); and iii) how the change is facilitated (*i.e.*, how and what supports the unit managers use to introduce, implement and sustain the new model) at the study sites.

## Methods/Design

A non-equivalent quasi-experimental before-after design is being used. Two sites have agreed to participate in the study. Multi-site sampling increases robustness by allowing for an assessment of comparisons and contrasts between the sites. Patient outcomes will be assessed at the time of discharge from inpatient rehabilitation and 6 months after discharge in cohorts of patients at both sites before and after implementation of the PCRM-CI model. The study has been registered at http://clinicaltrials.gov, Identifier NCT01566136.

### Setting and sample

The study is being conducted in two in-patient rehabilitation units at community rural sites. Site A is a 40-bed MSK rehabilitation unit in a 500-bed community hospital located 45 miles east of a large urban area. Site B is a 20-bed MSK rehabilitation unit at a small 120-bed community hospital. Ethics approval was obtained from both research sites and from Toronto Rehabilitation Institute.

The patient inclusion and exclusion criteria are: a) 65 years or older, b) admitted to rehabilitation directly from an acute care hospital after receiving surgery for a hip fracture; c) living in the community in a private home or residential setting (where an individual has services and supports but does not require 24 hour nursing care) prior to sustaining the hip fracture, d) able to speak and understand English; and e) have a family member or close friend who is familiar with the patient's pre-fracture condition and can act as a collateral informant. The patient exclusion criteria are: a) a pathologic hip fracture; b) a hip fracture associated with multiple trauma; and c) a previous hip fracture. All nursing staff, administrators and therapists caring for patients on the selected units will be invited to participate to assess their perceptions of the PCRM-CI. Written informed consent is obtained from both the patient and the caregiver/collateral informant at the first meeting following admission.

### Sources of data

Tables 2 and 3 list the quantitative and qualitative data we are collecting to meet the study objectives. In order to maximize the likelihood of observing a significant effect of the PCRM-CI model, we have selected outcome measures that have been shown to be sensitive to the model in our pilot work. We have focused our measurements at the point of discharge from rehabilitation and then at 6 months post-discharge, since recovery of ADLs often plateaus at this time [33].

**Table 2 T2:** List of patient measures collected

**Concept**	**Construct**	**Standardized Measure where applicable**	**Time of data collection**		
			**Admission**	**Discharge**	**6 months Post-Discharge**
**Factors Influencing outcomes**					
Patient					
Characteristics	Age	NRS	x		
	Sex	NRS	x		
	Level of education	Interview	x		
	Co-morbidities	NRS	x		
	Cognition	MMSE	x	x	
	Delirium	Confusion Assessment Method;	x	x	
		if Yes, Delirium Index	x	x	
	Pre-fracture functional status	OARS	x		
	Pre-fracture cognitive decline	IQCODE	x		
	Social Support	Interview	x		
**Process Measures**					
Treatment Fidelity	Follow clinical pathway	PCRM-CI Checklist	Daily for First Week of Rehabilitation		
**Patient Outcome Measures**					
Patients’ outcomes	1) Mobility & Locomotion	FIM – Mobility subscale (5 items) (3 items) + Locomotion subscale (2 items)	x	x	x
	2) Motor Function	FIM – Motor subscale (NRS)	x	x	x
	3) Living Situation	Interview		x	x

**Table 3 T3:** List of HCP measures collected

**Concept**	**Construct**	**Standardized Measure****where applicable**	**Time of Data Collection**	
			**Pre-PCRM-CI Implementation**	**Post-PCRM-CI Implementation (one year later)**
**Factors influencing outcomes**				
HCP Characteristics	Age	Questionnaire	x	
	Sex	Questionnaire	x	
	Level of education	Questionnaire	x	
	Job category	Questionnaire	x	
	Years practiced	Questionnaire	x	
	Years worked in the facility	Questionnaire	x	
	Type of work settings before being employed in this facility	Questionnaire	x	
**Process Measures**				
Treatment fidelity	Participation in workshop and education	Education Log	The APN will track staff training	
**HCP Outcome Measures**	Attitudes towards patients with CI	ADQ	x	x
	Job satisfaction	Job Satisfaction Scale	x	x
	Work-related stress	WSI	x	x
	Knowledge of dementia care	Dementia Quiz	x	x
**Determinants of RU**				
HCPs	HCPs’ feedback on the implementation of the PCRM-CI	4 focus groups		x
Unit Managers	Unit manager’s feedback on the implementation of the PCRM-CI	Semi-structured interviews	Every 2 months for the period of the 1 year implementation of the model	

#### Quantitative data

##### Patient characteristics

Age, sex, education level, cognitive status (Mini-Mental State Exam; MMSE) [34], pre-fracture cognitive decline (Informant Questionnaire on Cognitive Decline in the Elderly; IQCODE) [35], delirium (Confusion Assessment Method; CAM) [36], delirium severity for those with delirium (Delirium Index) [37], pre-fracture functional status (Older Americans Resources and Services Instrument; OARS) [38], co-morbidities (the number of medical diagnoses), and social support (living alone or with someone). Level of education, level of social support, OARS, and IQCDODE, are being collected from the collateral informant.

In this way, patient’s recall bias will not be a concern. Sex, age, and co-morbidities will be obtained from the National Rehabilitation Services (NRS) database, as these data are collected by all rehabilitation facilities in Ontario. MMSE, CAM and Delirium Index are being collected by the research associate (RA) on admission and at discharge. Every week the RA will also do a CAM to screen for delirium for every patient enrolled in the study because up to 61% of elderly patients post-surgery may become delirious during their stay [7].

##### Patient outcomes

Mobility and physical functioning outcomes will be collected by the RA. Living situation will be collected from the collateral informant.

a) Mobility, the main outcome variable, will be measured by the Functional Independence Measure (FIM) locomotion and mobility subscales, referred to as the FIMM [39]. These subscales measure the ability to walk and climb stairs and the ability to transfer in and out of bed, toilet, and tub/shower. The FIMM has well established reliability and validity and has been shown to have a high sensitivity for detecting functional improvement in patients across a spectrum of functional abilities and comorbidities [32,39,40].

b) Physical Functioning will be assessed with the motor-FIM [41], which is the most widely used scale to assess the function of patients with CI following hip fractures [6,15,42-44]. The motor-FIM scale has a high sensitivity for detecting functional improvement in patients with varying functional status and varying degrees of comorbidities and has been closely associated with the amount of care required by CI patients [45]. FIM data have been validated for caregiver proxy report [43] and for telephone administration [46].

c) Return rates to previous living situation: The living situation will be classified into 4 categories: i) discharge to private community setting including home alone, home with spouse, home with other; ii) retirement home; iii) nursing home; and iv) acute care hospital, as categorized in previous studies with CI patients following rehabilitation [43].

#### Heath care practitioner

##### Demographic characteristics

The age, sex, education, experience, job category, and length of time working on the unit will be recorded in a questionnaire. We anticipate that most, if not all, staff will be willing to participate because of the endorsement of our research by administrators at the two institutions and based on previous HCP recruitment rates for evaluation studies [47,48].

#### HCP outcomes

a) Attitudes: The Approaches to Dementia Questionnaire (ADQ) will be used to assess HCPs’ attitudes. Two subscales indicate the staff member’s degree of hopefulness about dementia and the extent to which a person-centred approach is espoused [49]. The subscales have good reliability and have been validated against direct observation of the quality of staff care interactions with patients [50].

b) Knowledge of Dementia: The Dementia Quiz will be used to measure the knowledge that HCPs have about dementia [51]. The subscales have moderate reliability (.63 for knowledge and .57 for coping) and have demonstrated predictive validity for staff experienced with caring for persons with dementia.

c) Satisfaction Working with Patients with Dementia: This measure includes 21 items assessing satisfaction; each item is scored from 0 (not at all) to 4 (extremely) and summed to create a total score ranging from 0 to 84. Reliability and validity of the scale have been demonstrated [52].

d) Work Stress Inventory (WSI): We will use a modification of this measure that is derived by averaging the frequency of 45 stressors, each scored 1 (never-not at all) to 5 (often-very well). Reliability and validity of the scale have been demonstrated [52]. The subscales are grouped into three domains; task stressors, relationship stressors, and system stressors.

#### Qualitative data

##### Qualitative sampling and data collection

We will use theoretical (also referred to as purposive) sampling for our qualitative methods of data collection. Theoretical sampling is a specific type of non-probability sampling in which the objective of explanation determines the specific criteria by which a sample is selected. Qualitative data collection for Advanced Practice Nurse (APN), HCPs, and unit managers includes:

i. APN: The APN will assess treatment fidelity of staff by recording workshop participation, the extent to which sessions were conducted as intended, and barriers and facilitators regarding the delivery of the in-services (*e.g.* group dynamics, comprehension of material).

ii. HCPs: We will conduct focus group interviews with a sub-sample of the HCP participants of the study. The purpose of these focus groups will be to understand how and why the model of care worked or failed, the need for refinement, and the factors important for replication. Specifically, the evidence adopted, the context, and the facilitation methods that influenced the implementation will be sought [53].

iii. Unit manager: Following the introduction of the new model of care onto the unit, semi- structured interviews will be conducted with the unit managers of the two sites every 2 months over the 1 year period. The purpose of the interviews is to probe the evidence based components of the PCRM-CI model that the sites replicated (*i.e.*, how individuals at the sites decide which components they will and can replicate), the context, and how the change is facilitated.

## Intervention

### The patient centred rehabilitation model targeting patients with CI

Staff will be introduced to 5 components of the PCRM-CI in a one-day workshop prior to implementing the PCRM-CI model. They will then be provided with 8 additional educational sessions throughout the year. A manual detailing all aspects of training, including specifics on how to present the material, ideas for stimulating discussion, and case vignettes to illustrate training concepts was developed for our pilot study and is being used for this study.

### PCRM-CI components

1) Rehabilitation management post hip fracture includes conducting physical and cognitive assessments at admission (functional assessment, pain, depression, premorbid functioning assessment), deciding on person-centred goals with the patient and family, setting a discharge date early, weekly team meetings to discuss methods of improving rehabilitation for the patients, and intensive interdisciplinary daily rehabilitation [54,55]. Intensive daily rehabilitation includes hip range of motion, lower extremity strengthening, and daily increase of ambulation distance using the lowest level of assistance/aids required, with careful attention to pain management [56]. Additional rehabilitation management includes providing advice, training, encouragement, drug treatments, and help with equipment and daily living aids. The physiotherapist and occupational therapist provide therapy once a day for 1 hour, 5 days a week. In addition, nursing staff walk the patient to the bathroom and/or dining room several times a day. A clinical pathway that was used during Phase 1 has been given to staff for their use.

2) Dementia management involves assessment of cognition using the MMSE within the first 3 days of admission to rehabilitation, and use of the REAP model in practice. For example, when patients become anxious, staff are asked to focus on the REAP for assessment and intervention solutions. Do staff approach the patient and introduce themselves and their purpose? Does the environment need to be manipulated, (*e.g.* therapy at the bedside *versus* the gym) during the first week in order to make it more conducive for the patient who has CI?

3) Delirium management involves assessment for its presence using the Confusion Assessment Method (CAM) within 3 days of admission to rehabilitation, assessing severity with the Delirium Index if it is found to be present, addressing pre-disposing factors, and managing symptoms of delirium using the REAP model (*e.g.*, reorient patient, encourage family involvement, use clocks, normalize sleep) [7]. A delirium protocol developed in Phase I will be given to staff. It includes the CAM and interventions to manage delirium.

4) Staff education and support is an integral component of the model of care and as such an APN in gerontology will be hired for 1 year at the time that the model is implemented. As the dementia and delirium care components of the program are new for most staff, the APN will help HCPs learn how to conduct the assessments and interventions at the bedside. Furthermore, since many of the patients have multiple comorbidities and are frail, additional 30 minute educational sessions are provided to enhance HCPs’ knowledge base about non-pharmacological sleep interventions, falls assessment and prevention strategies, pain management, bladder re-training and bowel management. Three additional non-clinical in-services will focus on team building, nursing rehabilitation standards of practice, and roles and responsibilities of team members. An additional responsibility of the APN will be to “grow an expert” within the facility in order to sustain the new model of care beyond the period of the study.

5) Individualized family support and education will be provided by the team and will be reinforced on admission to the unit with a brochure which includes the goals of the rehabilitation program. Additional written aids will be given to family members including: information on delirium, resources available once the patient is home, and a discharge booklet to prepare for going home.

### Data collection

Ethics approval was obtained at the sites and the RAs (one at each site) have been trained in data collection procedures by the PI and a clinical psychologist for the cognitive scales (MMSE, CAM, Delirium Index, and IQCODE) and by a co-investigator for the FIM scale. The RAs have also been trained to conduct interviews, to take field notes and to record factors that may influence the adoption of the model into practice. Each RA is responsible for recruitment, data collection, and data management for one institution.

The study is running at the same time in both facilities. Staff have been asked to participate within the first few months of the project. Recruitment of patients in the usual care group has taken one year. Following this period, the workshop developed in phase 1 was given to all HCPs on the unit. The criteria for admissions were then revised to allow a larger number of community dwelling patients with CI to be admitted. Eight additional educational sessions, described earlier, have been given to the staff during a three-month learning period. Recruitment of patients for the PCRM-CI model of care has commenced, and accrual will take 8 months.

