**Methods/Design:**

A non-equivalent pre-post design is being used to evaluate the PCRM-CI compared to usual care. All community dwelling (private home or retirement home) patients following a hip fracture are eligible to participate. Recruitment of both cohorts is taking place at two facilities. Target accrual is 70 hip fracture patients in the PCRM-CI cohort and 70 patients in the usual care cohort. We are also recruiting 70 health care providers (HCPs), who are being trained to implement the PCRM-CI, and their unit managers. Patient data are collected at baseline, discharge, and 6 months post-discharge from an inpatient rehabilitation program. Evaluations include mobility, physical function, and living arrangement. Additional outcome variables are being collected from medical records and from the patients *via* their proxies. Data on the prevalence and severity of dementia and delirium are being collected. Staff data are collected at baseline and one year after implementation of the model to determine change in staff knowledge and attitudes toward patients with hip fracture and CI. Bi-monthly semi-structured interviews with unit managers have been conducted to examine factors and barriers influencing the model implementation. Data collection began in 2009 and is expected to be completed in 2012. The control cohort of 70 patients has been recruited, and 45 patients have been accrued to the intervention group to date.

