## Background

A hip fracture is often a catastrophic event that results in significant impairment in mobility and function, and excessive institutionalization [1]. An estimated 25% to 75% of patients who are independent before their fracture can neither walk independently nor achieve their previous level of independent living within 1 year following the fracture [2]. Projections suggest that by 2041 the incidence of hip fractures in Canada will increase nearly four-fold [3], with an annual increase in economic burden of $2.4 billion per year [4], which is similar to other countries [5].

The course of hip fracture patients is often complicated by the presence of dementia and/or delirium. Dementia refers to a global loss of cognitive and intellectual functioning that gradually interferes with social and occupational performance [6]. Delirium is characterized by an acute decline in attention and cognition [7] and is linked to increased post-operative morbidity post-hip fracture [8]. Delirium may take weeks to months to diminish [9]. Both conditions are characterized by the presence of cognitive impairment (CI) across a spectrum of severity [8]. Two-thirds of cases of delirium occur in patients with dementia [10,11]. Studies have shown that 31 to 65% of older orthopedic patients have dementia and/or delirium [12]. As a result of the demographic shift to an aging population, the prevalence of dementia and the incidence of delirium in hip fracture patients are expected to progressively increase over the next 25 years [13]. In hip fracture patients, CI and low pre-fracture functional status are the most important predictors of poor prognosis regarding walking ability and return to independent living. [14].

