### Data analysis

Objective #1: The primary objective is to determine the impact of PCRM-CI on improvements in mobility (FIM locomotion and mobility) at discharge. At each site and for Usual Care and PCRM-CI groups, mobility is to be assessed at entry into rehab and at discharge from rehab. The change scores for patient outcomes will be compared with paired t-tests by cohort and site. In secondary analyses, multivariate regression will be used to examine the independent effects of each independent variable of interest on patient outcomes while controlling for other predictors and patient baseline factors**.**

Objective #2 (1 & 2): In the second instance, the mobility and physical functioning change scores and return to prior residence for Usual Care patients will be compared to those for PCRM-CI patients to assess the relative impact of the PCRM-CI model on outcomes for each site. Cross tabulations will be employed to assess rates of return to residence by rehab program and site. In particular, patients with CI are to be specifically targeted in the PCRM-CI model. We will compare means of mobility and physical functioning gains scores for patients with and without CI by program and site to assess the relative impact of the PCRM-CI model on patients with CI. In secondary analyses, multivariate regression will be used to examine the independent effects of each independent variable of interest on patient outcomes while controlling for other predictors and patient baseline factors**.**

Objective #2 (3): The introduction of the PCRM-CI model on the two units is meant to a) improve HCPs’ knowledge and attitudes toward working with hip fracture patients with CI, and b) measure the impact on provider satisfaction and work stress of working with these patients.

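### Admission criteria were widened between the cohorts to bring in more patients with CI, but the main comparison is unadjusted and the baseline-adjusted regression is ranked secondary, so the cohort contrast is confounded with case mix

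*Protocol article*

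**What the plan says.** The Methods/Design section describes the design plainly: "A non-equivalent quasi-experimental before-after design is being used". On timing, the Data collection section says "Recruitment of patients in the usual care group has taken one year"; the staff workshop came next, and then this change: "The criteria for admissions were then revised to allow a larger number of community dwelling patients with CI to be admitted". PCRM-CI recruitment followed.

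Study eligibility contains no CI criterion. The abstract says "All community dwelling (private home or retirement home) patients following a hip fracture are eligible to participate", and the criteria under Setting and sample agree. The CI mix of each cohort therefore follows whatever the unit admits.

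The Background says of hip fracture patients: "CI and low pre-fracture functional status are the most important predictors of poor prognosis regarding walking ability and return to independent living".

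For the primary objective, the Data analysis section says "The change scores for patient outcomes will be compared with paired t-tests by cohort and site". Under the secondary objectives, change scores and return to residence are set against each other by programme and site, with cross-tabulations for return. Mean gains are also compared for patients with and without CI. No covariates enter any of these. For both groups of patient objectives the section then adds: "In secondary analyses, multivariate regression will be used to examine the independent effects of each independent variable of interest on patient outcomes". That sentence goes on to say that other predictors and patient baseline factors are controlled for.

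**The concern.** The protocol changes the distribution of a factor it regards as strongly prognostic, in one cohort only, and then gives first rank to a comparison that takes no account of that factor. The difference between cohorts is then the sum of the effect of the care model and the effect of admitting a different mix of patients. A larger sample does not help, because the problem is bias and not imprecision. If the unadjusted and adjusted results disagree, the plan as written gives precedence to the confounded one.

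The affected outcomes matter: mobility gain is primary, and return to the community is the second outcome used to size the study.

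**Working it through.** **1. Reproduce the planned effect and sample size.** Inputs from the Sample size section: mean gains 7.2 and 12.1 (difference 4.9), SD 5.7, two-sided alpha 0.05, power 80%.
- Normal approximation: n = 2 × (5.7 × (1.960 + 0.842) / 4.9)² = 21.2, so 22 per group.
- Two-sample t-test: power is 79.5% at 22 and 81.4% at 23, so 23 per group. The stated 23, read as per group, reproduces.
- Return to community, 80% v 50%: 39 per group without continuity correction. This also reproduces.

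So 4.9 points is a fair yardstick for the bias.

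**2. Trace where case mix could be handled.**
- *Primary objective.* Its wording concerns patients with CI, but the Objective 1 analysis is not restricted to them and has no covariates.
- *Paired tests.* Read literally, paired t-tests describe change within a cohort and cannot compare two independent cohorts. The between-cohort comparison of mobility change is described under the secondary objectives. Neither is adjusted.
- *Means by CI status.* This comparison addresses a change in CI share. It is unadjusted, secondary, and does not address a change in CI severity within the CI group, which wider criteria may also bring.
- *Regression.* Planned with baseline control, ranked secondary, and worded around each variable of interest, without naming cohort as the quantity to be estimated.
- *The model itself.* Wider admission is not among the five listed PCRM-CI components, so the shift cannot be counted as part of the intervention as described.

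**3. Size of the bias.** Bias in the unadjusted contrast = (change in CI share) × (difference in mean gain between patients without and with CI). The protocol gives neither quantity. Both ranges below are assumptions.

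| Rise in CI share | Gap 2 points | Gap 4 points | Gap 6 points |
|---|---|---|---|
| 10 percentage points | 0.2 | 0.4 | 0.6 |
| 20 | 0.4 | 0.8 | 1.2 |
| 30 | 0.6 | 1.2 | 1.8 |
| 40 | 0.8 | 1.6 | 2.4 |

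As a share of the planned effect: 0.2 / 4.9 = 4% up to 2.4 / 4.9 = 49%.

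**4. Consequences at 70 per cohort, SD 5.7, two-sided t-test.**
- No true effect: the test rejects in 5.5% to 70% of studies instead of 5%.
- True effect 4.9, patients with CI gaining less: the expected contrast is 4.7 down to 2.5. Power falls from 99.9% to between 99.8% and 73%. Within one site (35 per cohort, equal split assumed) it is between 93% and 44%.
- Opposite sign: the contrast is inflated to between 5.1 and 7.3.

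**5. Price of adjusting for CI status.** Variance inflation = 1 / (1 − φ²), where φ is the correlation between cohort and CI status. With equal cohorts and CI shares p1 and p2, φ = 0.5 × (p2 − p1) / √(p̄(1 − p̄)). Shares are assumed.
- 30% to 50%: φ = 0.10 / √0.24 = 0.204, inflation 1.04, 24 per group.
- 30% to 70%: φ = 0.20 / 0.50 = 0.40, inflation 1.19, 28 per group.
- 20% to 60%: φ = 0.20 / √0.24 = 0.408, inflation 1.20, 28 per group.

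Power at 70 per cohort for 4.9 points stays at or above 99.5%.

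**The case against.** The best defence is that the plan already contains the remedy. Baseline-adjusted regression is planned for the primary and the secondary patient objectives, cohort may well be one of its variables of interest, and gains are also compared by CI status. If the primary population is patients with CI, as the primary objective suggests, a change in CI share does not bias the comparison at all. A detailed covariate list is normally left to the analysis plan.

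Much of this stands. It would be wrong to say that nothing in the plan separates the model from the case mix. The ranking remains: the article places unadjusted results first, and an analysis plan that follows it inherits that order. A CI-only comparison would still be open to a shift in severity, and the Objective 1 analysis does not say that it is CI-only.

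Three stronger readings are tempting and are not supported:
- *The bias is known to run against PCRM-CI.* The Background statement is about prognosis for walking and independent living. The primary outcome is a gain, and a lower admission score can leave more room to gain. The Background also cites evidence that patients with dementia and delirium can improve.
- *The CI share moved from 31% to 65%.* The Background gives those figures as a range across studies of older orthopaedic patients, not as before and after values on these units.
- *The regression would adjust away the model's own effect through discharge MMSE, CAM or Delirium Index.* Table 2 shows when these are collected. Nothing proposes them as covariates, and the Data analysis section speaks of baseline factors.

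**Conclusion.** The point holds as one of ranking and specification. The documents establish that the admission criteria changed between the cohorts, that the change was meant to raise the number of patients with CI, that the protocol regards CI as strongly prognostic, and that the leading comparisons are unadjusted. The main cohort contrast is therefore confounded with case mix.

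The direction is probably unfavourable to PCRM-CI, most plausibly for return to the community, where the prognostic statement applies directly; for mobility gain the sign is uncertain. The range of 0.2 to 2.4 points rests wholly on the assumed shift and gap, and covers CI share only. A severity shift would add to or offset it by an amount that cannot be calculated from the protocol. A reader might infer that an effective model would be made to look useless or harmful. The figures do not show that: even at the extreme of the assumed range, a true 4.9 still appears as 2.5, with 73% power when sites are pooled.

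**What to change.** - Prespecify as primary the between-cohort effect from a linear regression of discharge FIMM on cohort, admission FIMM, site, admission MMSE, admission CAM, IQCODE, OARS, age and number of comorbidities. Use admission values only.
- For return to the community, use logistic regression with fewer covariates. At the planned rates, 70 × 0.50 + 70 × 0.20 = 49 patients would not return; nine coefficients would leave about 49 / 9 = 5.4 events each.
- State whether the primary population is all enrolled patients or those with CI.
- Report CI share and severity at admission by cohort. Keep the unadjusted comparison as supportive.
- Optionally, repeat the comparison leaving out PCRM-CI patients who would not have met the earlier admission criteria. The article gives neither set of criteria, so whether charts allow this is unknown.

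**Cost.** Mainly wording: Table 2 already collects every covariate at admission except site, which is known. Adjusting for CI status inflates the variance by about 1.04 to 1.20 under the assumed shares. Other covariates that differ between cohorts would add to this, while prognostic ones reduce residual variance; against a need of 24 to 28 per group, 70 leaves ample room. The Discussion reports 45 of 70 intervention patients enrolled, so the change can be fixed before the cohorts are compared.
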